### Data Collection—Experiment

Recruited participants will have access to the final DCE instrument invited by the research team or any citizen researcher. After reading and agreeing to participate, they will answer both choice settings, following the structure of each one previously described in this paper.

All collected data will be stored in a cloud (Google Drive) and anonymized by the study coordinator in the team ([name]) using random numbers. Only this researcher will access the identified data and the identified informed consent forms. The research team will work on the anonymized dataset. At the end of the study, all collected anonymized data will be downloaded for data analysis, and any record from any virtual platform will be deleted. Finally, data will be available online in an appropriate institutional repository after the publication of the final results. Missing data will be identified, and the method of conditional imputation will be used, considering an appropriate regression model according to the type of variable to be imputed.

### Analysis plan

An analysis plan for this protocol is prepared and made available in the DMPHub, using the DMPtool [33].

#### Qualitative analysis

The framework method will be used for performing a qualitative content analysis [34]. Data organization and analysis will follow a predefined sequence [28]: (1) editing material, which comprises the organization of the data collected and the creation of the subgroups (such as private clinical practice dentists, and knowledge translate researchers); (2) free-floating reading, reading the collected data freely, with no intention of categorizing to understand the general context; (3) construction of the units of analysis, reading each excerpt and conducting the first preliminary codes of meaning and group together the speeches that suggest the same meaning (Maxqda® software can assist in the coding); (4) identification of cores of meaning, re-reading of the previously identified grouped speeches, to give them a code (entitling them), (5) consolidation of categories, refining the codes; (6) discussion of the topics with the group and the literature; (7) validity, considering the research question.

#### Quantitative and statistical analysis

The characteristics of the respondent sample will be examined against the known characteristics of the population whose preferences researchers may want to generalize. We will use appropriate tests to examine the hypothesis that the respondent sample has been drawn from the desired population. Additionally, we will compare the sample recruited by the traditional and citizen science approach to verify any possible differences and, eventually, explore or adjust any subsequent analysis.

The validity of the data will be checked considering response error (included in the set of choices to detect internal validity failures). For that, we will analyze the occurrence and the frequency of the respondents who always or nearly always choose the alternative with the best level of one attribute, and preferences dominated by a single attribute. Any failure of internal validity detected will be statistically controlled in further analyses.

From the main DCE, we expect to estimate the strength of preferences for the attributes included in the survey. We also expect to demonstrate how choice probabilities may vary with changes in attributes or attribute levels.

At a first attempt, the probability of choice for each attribute (and its respective levels) may be calculated. Data generated by the DCE will be coded for further analysis. We will adopt the dummy-variable coding as the option for categorical coding of attribute levels [35]. Conditional logistic regression and latent-class finite-mixture models will be used to estimate average preferences (the probability of choice) across a sample considering two alternatives and attributes and levels, as well as heterogeneous effects on choices across a finite number of groups or classes of respondents. We will assume that multiple observations from the same respondent are independent [36]. Another purpose of such statistical analyses might be to estimate how preferences vary by individual respondent characteristics. Multinomial regression models will be used to relate respondents’ choices to respondents’ personal and professional characteristics (respondents’ profiles) [36]. For goodness-of-fit, the likelihood ratio chi-square test will be calculated for each model to provide a way to determine whether the inclusion of attribute-level variables significantly improves the fit of the model compared to a null model.

Subgroup analysis considering different federative units and types of practice (public or private) will be performed to explore possible differences among different groups that demand future individualization of implementation processes.

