### Settings

The DCE instrument will be self-administered and delivered in a virtual environment. The computerized approach has already been used in previous studies measuring preferences [25]. This strategy is also reported as an alternative by the World Health Organization guidelines for conducting DCEs [26].

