### Instrument properties

The template (electronic form) to be responded by the participants will include the Informed Consent Form, a preliminary questionnaire to capture participants’ information, and the DCE instrument by itself, containing the choice sets defined according to the steps described in the next sections.

The questionnaire will collect participants’ data such as gender, age, position (dentist, manager, coordinator), place of residence and work (Federative Unit of Brazil), year of graduation, and graduate courses (completed or not).

The DCE instrument will consist of two choices-sets with pairs of unlabeled alternatives (binary forced-choice experiment). Each choice-set comprises a different clinical decision context (Fig. 2).

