By the end of the panellist discussions, the coordinator board ([name], [name], [name], [name], [name]) will be gathered to refine the list generated, preserving the previously given contributions. The final attributes and levels list will be finally sent to all panellists, and each level’s approval rate will be registered. To be approved, final levels and attributes must be approved by the most representatives in the panel (at least 80% of approval). If this approval rate is not achieved, all panellists’ views about such a specific disapproved level will be reconsidered.

Phase 2**—Determination of the experimental design**—At this stage, the aim was to produce a number of pairs of alternatives, combining the levels of the attributes. The experimental design is a manner to combine these pairs for each choice set in the most efficient arrangement of the pairs of alternatives, aiming not to use all possible combinations (cognitively impossible), but a number enough to permit the preference to be measured. The more attributes and levels (more sets of choices) used, the greater the complexity of the experiment and, consequently, the more significant unobserved variability we must consider in the analysis [18]. A list with minimum but enough combinations will be generated at the end. We will exclude alternatives with implausible combinations of unbalanced choice levels and sets to adjust the experiment, ensure the plausibility of the choices, and reduce hypothetical bias (when the hypothetical nature of the questions results in biased answers). The design efficiency (Efficiency D) will be calculated to determine if the number of pairs can assess the possible effects (preference) intended to be measured. These calculations will be performed using the Ngene software [17, 19, 30].

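### The only response-error check spelled out is single-attribute dominance, which most random or same-side responders pass and which the Discussion treats as a genuine preference

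*Protocol article*

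**What the plan says.** In Quantitative and statistical analysis the protocol states: "The validity of the data will be checked considering response error (included in the set of choices to detect internal validity failures". The next sentence gives the method. It will count "respondents who always or nearly always choose the alternative with the best level of one attribute" and look for "preferences dominated by a single attribute". No threshold is given for the second half of 'always or nearly always'. The paragraph ends: "Any failure of internal validity detected will be statistically controlled in further analyses".

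The setting matters. Under Settings: "The DCE instrument will be self-administered and delivered in a virtual environment". Under Instrument properties the format is a "binary forced-choice experiment", so there is no opt-out. The stated output of the main analysis is that "we expect to estimate the strength of preferences for the attributes included in the survey", along with how choice probabilities change with the attributes.

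Phase 2 of Instrument development adds: "We will exclude alternatives with implausible combinations of unbalanced choice levels and sets". Questions on difficulty and completion time are described for the pilot form only.

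**The concern.** The aim and the measure do not match. Response error in an online choice survey mostly means answering at random or always clicking the same side. Neither follows an attribute, so neither tends to look like dominance. A dentist who truly cares mainly about one attribute does look like dominance. The Discussion describes exactly that respondent, one who keeps choosing the low-cost option, as showing the preference the experiment is meant to reveal. The rule therefore risks labelling signal as error and letting error through.

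Because choices are forced and self-completed, an inattentive respondent still leaves a complete record. That record enters the conditional logit model with full weight. At stake are the absolute strength of preference, the predicted choice probabilities, precision, and the planned comparisons by federative unit, type of practice and recruitment route.

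**Working it through.** **Figures in the plan.** The check itself has no stated figure. The sample-size rule reproduces: 10 × 6 + 50 = 110 respondents, and 110 × 1.2 = 132. Six is the maximum number of attributes named under Participants. The number of pairs, the levels, the true weights and the inattentive share are not in the document and are assumed below.

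**1. Chance that a random clicker is flagged, full contrast.** Assume six two-level attributes that differ in every pair, are mutually balanced, and are flagged when the best level is chosen in all n pairs or all but one. For one attribute the probability is (n + 1)/2^n. Two balanced attributes disagree in n/2 pairs, so one answer pattern cannot meet the rule for both, and the total is 6(n + 1)/2^n.

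- n = 8: 54/256 = 21%
- n = 12: 78/4096 = 1.9%
- n = 16: 102/65536 = 0.2%

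**2. The same question when attributes differ in about half of the pairs.** Simulation: 110 respondents, 12 pairs, true weights 1.0, 0.8, 0.6, 0.5, 0.4, 0.3. A respondent is flagged if the best level of any attribute is chosen in at least 90% of the pairs where it differs (at least four such pairs).

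- Random clickers flagged: 10-13%
- Same-side clickers flagged: 10-12%
- Attentive trade-off respondents flagged: about 34%

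So about 87-90% of careless respondents pass, and attentive ones are flagged more often than careless ones.

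**3. Effect of undetected random answers on the coefficients.** If a share q answers at random, an observed choice probability becomes (1 − q)p + q/2. For a single pair at q = 10%:

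- p = 0.75: 0.725; log-odds 1.099 becomes 0.969, 12% lower
- p = 0.90: 0.86; 2.197 becomes 1.815, 17% lower
- p = 0.95: 0.905; 2.944 becomes 2.254, 23% lower

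Fitting the six-attribute logit to these mixed probabilities gives the following loss.

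| Design and weights | q = 10% | q = 20% |
|---|---|---|
| Half contrast, weights as in step 2 | 14% | 26-27% |
| Full contrast, same weights | 17-18% | 30-32% |
| Full contrast, weights doubled | 30-31% | 47-48% |

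Simulations over designs of this kind gave 13-32% at 10% and 26-47% at 20%. In the step 2 design, same-side clickers cost nearly the same as random clickers.

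**4. Relative importance.** In the step 2 simulation the largest attribute's share of the summed coefficients is 0.278 in truth and 0.274-0.281 at every inattentive share from 5% to 30%. The loss is close to proportional, so shares and ratios hold. An extreme case moves more. With one weight of 3, five of 0.5 and full contrast, the top share goes from 0.55 to 0.61 at q = 10%.

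**5. Group comparisons.** Take two groups of 55 with identical true preferences (step 2 weights, 12 pairs), 5% inattentive in one and 25% in the other. Coefficients come out at about 0.94 and 0.68-0.69 of true. A 5%-level likelihood ratio test of equal coefficients rejects in about 31-32% of runs, against about 5-7% when inattention is equal.

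**The case against.** The strongest reply is that the parenthesis in the validity sentence may announce test items built into the choice sets. The separate analysis plan and final questionnaires are not shown, and an article may leave such items to them. This stands in part: one cannot conclude that no check items exist. But the article does not leave the method open. It says how response error will be examined, and that method is dominance.

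Four stronger readings are tempting and are not supported.

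- A reader might infer that every preference result is diluted. Research questions 1 and 2 ask for relative importance and trade-offs, and step 4 shows these largely survive when inattention is unrelated to preference.
- A reader might infer that Phase 2 deletes the pairs that would reveal an error. That sentence is unclear, its stated aim is plausibility, and it does not mention pairs with a clearly better option. Removal is a risk only.
- A reader might infer that same-side clickers are never flagged. That needs best levels to be exactly balanced between sides, which is not stated; in step 2, 10-12% were flagged.
- A reader might infer that careless respondents necessarily stay unseen. The plan compares recruitment routes and may adjust for differences, and its latent-class model could absorb a class with near-zero preferences. The text does not assign the model that role.

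The inattentive shares are assumptions, and nothing in the document shows that inattention differs between groups.

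**Conclusion.** The point holds in this form: the stated response-error check is aimed at the wrong pattern. It misses most random or same-side answering under the designs tried (the exception is short full-contrast designs, where the catch rises to 21% at 8 pairs), and it flags behaviour that the Discussion counts as preference. The consequence is attenuation of coefficients and choice probabilities, roughly 13-32% at an assumed 10% inattentive, and possible false subgroup or recruitment-route differences if inattention is uneven. The two main research questions lose mainly precision. The sizes rest on assumed designs, weights and inattentive shares. The mismatch between aim and measure does not. It should be corrected before the instrument is final, because check tasks cannot be added after data collection.

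**What to change.** In each hypothetical set (choice set 1 and stage (a) of choice set 2), include one pair in which one option is better on every attribute and one repeat of an earlier pair. Keep both out of model estimation. State in Phase 2 that the exclusion of unbalanced sets does not apply to the check pair. If check items already exist, describe them.

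Define response error as failing these tasks or choosing the same side throughout. Report single-attribute dominance separately, as a preference pattern. Present estimates with and without flagged respondents.

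A random clicker fails at least one of the two tasks with probability 1 − 0.5 × 0.5 = 75% per set, and 1 − 0.25² = 94% over two sets. An attentive dentist can also change answer on a repeat: at a choice probability of 0.9, 2 × 0.9 × 0.1 = 18%. The comparison should therefore be a sensitivity analysis, not an exclusion rule.

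Cost: two extra choices per set, a slightly longer form, and one extra analysis.

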### Participants

Our sample will comprise Brazilian oral health professionals who agree to participate in the study. As the application will be through an online platform, those who do not have access to a device such as a smartphone, tablet, computer and/or do not have access to the internet will not be able to participate.

The recruitment strategy will target dentists from both the public and private sectors. Health Departments from different states in Brazil will be contacted as facilitators to organize an application day for the public sector. Local events (congresses and commercial meetings) will be used to recruit participants from the private sector. Participants enrolled in this study will be invited to become citizen researchers and, after a training, apply the same instrument to their peers (other dentists) in their community. This approach will be used to achieve participants from different parts of Brazil and not only those who are close to research centers [20, 21].

Participants who consent to become citizen researchers will receive training to calibrate them both in ethical aspects and methodological aspects, guaranteeing the integrity and autonomy of the participants who will be recruited by them as well as the scientific confidence and rigor of the data collected [20, 22]. Individual and collective targets will be defined for the citizens research considering the number of dentists supposed to be achieved with this strategy of citizen science. A monitoring platform will be created [23] to motivate data collection and establish communication between investigators and citizen researchers.

The sample size will be calculated based on an arbitrary rule summing up 10 respondents for each attribute defined for the DCE and extra 50 participants [24]. By anticipating a maximum of six attributes in the experiment, we expect that a sample of 110 respondents would be needed to provide sufficient statistical power based on the rule described above. An additional number of participants will be increased in sample size for compensating possible a 20% non-respondent rate, totalizing an anticipated minimum sample of 132 dentists. After defining the attributes, this calculation will be adjusted, if necessary.

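### The latent-class model is meant to group dentists, yet the plan assumes without qualification that one dentist's choices are independent, which removes the information that identifies the classes

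*Protocol article*

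**What the plan says.** Under Quantitative and statistical analysis, the protocol article names two models in one sentence: "Conditional logistic regression and latent-class finite-mixture models will be used to estimate average preferences". The same sentence gives the purpose of describing "heterogeneous effects on choices across a finite number of groups or classes of respondents". The sentence that follows is "We will assume that multiple observations from the same respondent are independent", with a literature citation and no qualification.

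Four other statements bear on the point:

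- Instrument properties: choices are forced, between two unlabelled alternatives.
- Participants: "By anticipating a maximum of six attributes in the experiment, we expect that a sample of 110 respondents would be needed".
- Instrument development, Phase 2: "A list with minimum but enough combinations will be generated at the end". D-efficiency will be used "to determine if the number of pairs can assess the possible effects (preference) intended to be measured". Classes are not mentioned there.
- Quantitative and statistical analysis: attribute levels are dummy coded.

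The number of pairs, the number of levels per attribute and the number of classes are not fixed.

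**The concern.** A class of respondents means that a dentist has one class, and therefore one set of preferences, across all tasks. Choices are then independent given the class but dependent once the unknown class is averaged over. The plan states independence without that condition, directly after naming the latent-class model.

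An analyst who followed the sentence literally would fit the mixture to single choices with no respondent identifier. That fit classifies choices rather than dentists. It may have no unique solution, or it may return unstable classes where distinct groups of dentists exist. Wider standard errors would not repair this, because the fault lies in the likelihood itself.

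**Working it through.** **Inputs from the protocol article.** At most six attributes and 110 respondents (Participants); binary forced unlabelled choices (Instrument properties); dummy coding (Quantitative and statistical analysis). The stated sample size reproduces: 10 × 6 + 50 = 110, and 110 × 1.2 = 132.

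**Assumptions, not in the protocol.** Two or three levels per attribute; two classes; class share π = 0.5; class coefficients drawn around 0.6 in one class and −0.2 in the other (log-odds scale); 6 to 48 distinct pairs J; no constant term.

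**Step 1: classes imply dependence.** Let p1j and p2j be the probabilities of choosing the first alternative of pair j in classes 1 and 2. For one dentist and two pairs j and k,

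Cov(Yj, Yk) = π(1 − π)(p1j − p2j)(p1k − p2k).

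This is non-zero whenever the classes differ on both pairs. Unconditional independence therefore contradicts the existence of such classes.

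**Step 2: the literal likelihood.** With every choice independent, each has probability qj = π p1j + (1 − π) p2j. The likelihood is the product over pairs of qj^sj (1 − qj)^(N − sj), where sj is the number of dentists choosing the first alternative. Only J shares enter, so at most J parameters can be identified, however large N is.

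**Step 3: parameters needed.** With C classes and K coefficients per class, the count is C × K + C − 1.

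- Two levels, K = 6 × 1 = 6: two classes need 2 × 6 + 1 = 13; three need 3 × 6 + 2 = 20.
- Three levels, K = 6 × 2 = 12: two classes need 2 × 12 + 1 = 25; three need 3 × 12 + 2 = 38.

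**Step 4: the respondent-level likelihood.** A dentist contributes π Πj P1(yj) + (1 − π) Πj P2(yj). This uses whole response patterns, of which there are 2^J − 1 free probabilities. At J = 6 that is 2^6 − 1 = 63, against 13 parameters.

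**Step 5: numerical check.** Rank of the Fisher information and median standard error (SE) of the class coefficients, two classes, N = 110:

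| Levels (parameters) | Pairs J | Literal: rank | Literal: SE | Respondent-level: rank | Respondent-level: SE |
|---|---|---|---|---|---|
| 2 (13) | 6 | 6 | none | 13 | 0.52 |
| 2 (13) | 8 | 8 | none | 13 | 0.23 |
| 2 (13) | 10 | 10 | none | 13 | 0.18 |
| 2 (13) | 12 | 11 | none | 13 | 0.16 |
| 2 (13) | 13 | 13 | 6.42 | 13 | 0.14 |
| 2 (13) | 16 | 13 | 1.23 | 13 | 0.15 |
| 2 (13) | 20 | 13 | 0.84 | 13 | 0.11 |
| 2 (13) | 24 | 13 | 2.19 | 13 | 0.09 |
| 2 (13) | 25 | 13 | 0.43 | 13 | 0.10 |
| 2 (13) | 32 | 13 | 0.39 | 13 | 0.08 |
| 2 (13) | 48 | 13 | 0.40 | 13 | 0.06 |
| 3 (25) | 16 | 16 | none | 25 | 0.23 |
| 3 (25) | 24 | 24 | none | 25 | 0.14 |
| 3 (25) | 25 | 25 | 1.36 | 25 | 0.14 |
| 3 (25) | 32 | 25 | 0.76 | 25 | 0.12 |
| 3 (25) | 48 | 25 | 0.40 | 25 | 0.09 |

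Where both likelihoods have full rank, the SE ratio runs from 0.43/0.10 = 4.3 to 6.42/0.14 ≈ 46.

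The rank bound does not depend on the coefficients or class share. The SEs do. Each row rests on one design and one coefficient draw, which is why they do not fall steadily with J, so they show order of magnitude only.

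**The case against.** The strongest reply is that the sentence is loose wording. Independence given class is the usual latent-class assumption, the sentence before it speaks of classes of respondents, and the clause may have been meant for the conditional logit, named first. On either reading the likelihood is per dentist and can be estimated with few pairs. The cited source cannot be consulted here. This reply lowers the severity but does not remove the point: the text states an unqualified rule after naming both models, and an analyst could follow it.

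A reader might infer that the classes cannot be estimated under this plan. The document does not support that. Phase 2 asks for a list that is minimal but also sufficient, and fixes no number of pairs. From 13 or 25 pairs the two-class model reached full rank even on the literal reading. Six attributes is a maximum: with five two-level attributes two classes need 2 × 5 + 1 = 11 parameters, which the bound does not exclude at 12 pairs. Sufficiency is, however, judged by D-efficiency for the preference effects, and 6 or 12 such effects call for fewer pairs than 13 or 25 class parameters.

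A reader might also infer that tailored implementation rests on the latent classes alone. It does not. The article ties individualised implementation to the subgroup analysis by federative unit and type of practice, and also plans multinomial models on respondent characteristics.

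Finally, a separate analysis plan exists and may give the likelihood in full. That would excuse a missing detail, but this is a stated assumption that conflicts with the model's stated purpose.

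**Conclusion.** Wrong as written; moderate severity. Latent classes of dentists and unconditional independence of a dentist's choices cannot both hold, and following the second discards what the first needs.

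On the literal reading with six attributes, two classes are not identified below 13 distinct pairs (two levels each) or 25 (three levels), whatever the number of dentists. Above those thresholds precision is several times worse or more: at 48 pairs the median SE is 0.40 against 0.06 (two levels) or 0.09 (three levels).

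The thresholds rest on the assumed levels and number of classes; the SEs also rest on assumed coefficients, class share and designs. Because the protocol fixes none of these, non-identification is a conditional risk. If conditional independence was intended, the fault is confined to the wording.

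**What to change.** Replace the independence sentence with: 'In the latent-class model, class membership is fixed per respondent and choices are independent only conditional on class; the likelihood contribution of a respondent is the class-weighted sum of the product of his or her choice probabilities.' Declare the respondent as the panel unit in the software, and make the separate analysis plan agree.

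If an independence assumption is kept for the conditional logit, say that it applies to that model only. How its standard errors should allow for repeated choices is a separate question.

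The cost is one sentence and one panel-identifier setting. It needs no new data and no change to the sample size or instrument, and should be settled before the analysis.

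### The ordinary likelihood-ratio chi-square test against a no-attribute null, planned for every model, has no valid reference distribution for the latent-class models

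*Protocol article*

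**What the plan says.** The section Quantitative and statistical analysis of the protocol article names two families of choice model: "Conditional logistic regression and latent-class finite-mixture models will be used to estimate average preferences". The latent-class part is there to capture "heterogeneous effects on choices across a finite number of groups or classes of respondents". The number of classes is not given.

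One fit criterion is then stated for all of them: "the likelihood ratio chi-square test will be calculated for each model". Its purpose is to see "whether the inclusion of attribute-level variables significantly improves the fit of the model compared to a null model". The same section adds: "We will assume that multiple observations from the same respondent are independent". The article also refers to a separate analysis plan held in an online repository, which is not shown.

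**The concern.** The criterion covers every model, so it covers the latent-class models. The ordinary chi-square reference for a likelihood-ratio test needs all parameters of the larger model to be identified under the null. A finite mixture breaks that condition. When no attribute affects choice, every class has the same zero coefficients and any split of respondents between classes gives the same likelihood. The test can then reject far too often, even for the limited question the plan asks of it, namely whether the attributes add anything.

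There is also a point of interpretation. The comparator has neither attributes nor classes, so a small p-value for a two-class model may reflect a preference that all dentists share. It should not be cited later as support for the classes.

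**Working it through.** **Inputs from the protocol article.** The choices are "pairs of unlabeled alternatives (binary forced-choice experiment" ones (Instrument properties). The sample size rests on at most six attributes (Participants): 10 × 6 + 50 = 110, which reproduces the stated figure before the allowance for non-response. The article gives no significance level, degrees of freedom, number of tasks, levels or classes for the fit test.

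**Assumptions.** Alpha 0.05; two classes; 12 or 16 binary tasks; p = 6, 10 or 12 coefficients. Six attributes at three dummy-coded levels give 6 × (3 − 1) = 12.

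**Formulas.** With N respondents and T tasks, the null gives each alternative probability 0.5, so its log-likelihood is −N·T·ln 2. The statistic is LR = 2(log-likelihood of model − log-likelihood of null). Counted degrees of freedom are p for the conditional logit and 2p + 1 for two classes (two sets of coefficients and one class share): 13, 21 and 25 for p = 6, 10 and 12.

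**Step 1: no attribute matters and there are no classes.** Rejection at nominal 5%, N = 110:

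| Tasks | p | df, two-class | Conditional logit | Two-class |
|---|---|---|---|---|
| 12 | 6 | 13 | 3.7% | 18% |
| 16 | 10 | 21 | 4.5% | 34.5% |
| 12 | 12 | 25 | about 5% | 32.5% |
| 16 | 12 | 25 | about 5% | 45.5% (43% in a second run) |

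The first row has 300 samples, the second 200, the others 150 to 200. The Monte Carlo standard error is √(0.18 × 0.82/300) = 2.2 points in the first row and √(0.345 × 0.655/200) = 3.4 points in the second. A further check gave 19% with 6 and 43% with 12 coefficients, against 2.5% to 5% for the conditional logit.

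The mean statistic shows the same thing, since a chi-square variable has a mean equal to its degrees of freedom. For the conditional logit the means were 5.8 (df 6) and 9.8 (df 10), as they should be. For two classes they were 17.7 (df 13) and 30.3 (df 21).

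All choices in this step were generated independently, so the inflation does not come from the plan's independence assumption.

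**Step 2: one shared preference and no classes** (12 tasks, p = 6). With one attribute at log-odds 0.5, the two-class test rejected in 98.7% of samples and the conditional logit in 98.7%. With all six at 0.4, both rejected in 100%. In the first case the mean statistic was 59.1 for two classes, of which the one-class model already supplied 47.4 (47.4/59.1 = 80%). In the second it was 144.3 of 155.7 (93%).

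**Step 3: two equal classes with opposite preferences (±0.6).** The two-class test rejected in 100%, the conditional logit in 11%. Here the rejection does come from the classes.

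**Step 4: two classes against one with the ordinary chi-square (df p + 1).** Under homogeneity this rejected in 27% (p = 6) and in 60% to 65% (p = 12, 16 tasks). The simulated 95% critical value for p = 12 was 32.0 (12 tasks) and 36.5 (16 tasks), against 22.4 from chi-square with 13 df. Changing the comparator alone therefore does not repair the test.

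**Step 5: the alternatives** (p = 12). At 16 tasks, BIC against one class chose two classes in 0% of homogeneous samples. With two clearly different classes, a simulation-calibrated test of two against one class found them in 100% and BIC in 93% to 100%. With moderately different classes, the calibrated test had 49% to 76% power.

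**The case against.** The strongest reply is that the test is faulted for a job it was not given. The article uses it to judge whether attribute levels improve fit. Where dentists share a preference, rejecting the null is the correct answer, so the near-100% rejection in step 2 is power and not an error rate. This stands.

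A reader might infer that the plan would use the test to establish or count classes, and that spurious groups would then shape the implementation strategy. The document does not support that. It gives the test no such role. It relates preferences to observed respondent characteristics by multinomial regression, and it links tailoring of implementation to subgroups by federative unit and by public or private practice, not to latent classes. A rule for the number of classes may be in the analysis plan that is not shown, so its absence here is not a fault. A reader might also infer that the test never responds to real classes; step 3 shows that it can.

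A second reply is that the inflated error rate of step 1 arises only if no attribute affects any choice. That is unlikely for attributes drawn from the literature and approved by at least 80% of a panel, and the conditional logit test would usually expose such a case. This limits the practical harm. It does not make the stated reference distribution valid, and a class-number rule elsewhere would not do so either.

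**Conclusion.** The point holds in a limited form. The article assigns an ordinary chi-square test to a model for which that reference distribution is wrong, even for the test's own stated purpose. With no attribute effect, the two-class test rejected in roughly 18% to 46% of simulated samples instead of 5%; the conditional logit test held about 5%. The size of the inflation depends on the assumed tasks, levels and two classes, none of which the article fixes. The direction was the same in every setting tried.

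A significant result against the null is in addition not specific evidence that preference classes exist. That is a caution about later interpretation, not a claim the protocol makes.

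**What to change.** Limit the chi-square test against the null model to the conditional logit. For the latent-class models, wording such as this would do: *Fit is judged by BIC, comparing K classes with K−1 classes and with the one-class conditional logit. A parametric-bootstrap likelihood-ratio test of K against K−1 classes supports the choice. The comparison with the no-attribute null is not cited as support for classes.* The plan should also state beforehand which of the two decides if they disagree. The ordinary chi-square should not be used for K against K−1, for the reason in step 4.

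If the separate analysis plan already has such a rule, it is enough to narrow the reach of the chi-square test in the article and refer to that rule.

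The cost is a sentence or two and some computing time, with no new data. The downside is that BIC is conservative when classes differ only moderately, so fewer classes may be reported. The conditional logit test alone can also miss attributes on which dentists hold opposed views (11% rejection in step 3); the comparison of two classes with one covers that case.
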